#### **IV. Research Methods**

##### **A. Outcome Measure(s):**

HOMER is a randomized comparative effectiveness research study to compare differences in short-term and long-term outcomes in patients who begin medication assisted treatment (MAT) for opioid dependence or opioid use disorder (OUD) with an unobserved induction (home induction) or an observed (office-based) induction. The primary outcomes are:

1. Number of days of buprenorphine treatment between day one and day 270 of treatment
2. Number of days of use of illicit opioids between day one and day 270 of treatment.
3. Percent of patients in each group who took buprenorphine on  $\geq 80\%$  of the days between day one and day 270.
4. Percent of patients in each group using illicit opioids on  $< 10\%$  days from induction to nine-month follow-up.
5. Quality of life and social functioning

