### *Participant Recruitment*

- Patients

This study will enroll patients that the primary care provider believes would benefit from MAT with buprenorphine. As this study will occur with the patient's health care medical provider, the recruitment for participation in this study will occur in accordance with guideline-concordant screening, as part of usual care, by the practice care team to identify patients with OUD and patients with chronic pain that have opioid dependence and could benefit from MAT with buprenorphine. Primarily these are patients with opioid dependence and either 1) addiction as defined by DSM-V criteria for OUD and/or 2) chronic pain with long-term, high dose opioid use (greater than one year and morphine equivalent daily dose higher than recommended by the CDC). Participating practices will describe the options for induction (office or home) to patients who are opting to receive MAT, which is part of their usual care. Patients who are willing to use either type and meet criteria will be informed of the study verbally and given a study information sheet. If the patient is interested and willing to learn more about the study at that visit, referred here to as Time 1, the practice will call the central study team staff, who will describe the study in detail to the patient, including that participation involves randomization to office-based or home induction. If the patient is interested in participating, the study team staff will confirm eligibility, consent the patient, randomize the patient to the *office-based induction* arm or the *home induction* arm, and contact the practice with the study arm.

This study aims to enroll 1200 participants to reach a goal of 1000 retained participants receiving MAT (allowing for attrition prior to MAT induction). In Colorado, enrollment goals are 660 to retain 550 receiving MAT. We anticipate an average of 10 patients per practice will be screened for OUD or identified as opioid dependent, accept MAT induction, enroll in the study (accepting randomizing into home or office-based induction), and have monitoring data entered into the Practice Participant Tracker.

- Practice Clinicians and Staff

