### Randomization

Patients who meet eligibility criteria and consent to participate will be randomized to either the *office-based induction* arm or the *home induction* arm. Both induction methods are evidence-based approaches for initiating MAT in patients with OUD. Participating practices will receive a suggested protocol for both office-based and home inductions. However, practices and providers experienced in MAT may have their own existing protocols for office and home induction. Given the pragmatic nature of this trial, we will allow some variation in induction protocols.

Randomization will occur at the patient level. Patients will be informed that participation includes randomization by the initial information handout they receive from the practice and again by the research team member during the consent process. Randomization will occur immediately following consent. A study coordinator will inform the participant of their randomization assignment. As consent will be completed by phone with the patient, the study team member will inform the participant of the study arm assignment (randomization result) while on the phone with the participant and then immediately inform the practice of the patient's assigned induction type.

A block randomization process will be used where patient participant "slots" will be randomized for each practice in advance of recruitment to ensure equal distribution between arms at each practice. This will increase our power to detect differences between study arms, as opposed to a cluster randomized trial. Further, this use of block randomization will provide the best opportunity for each practice to enroll patients in either arm of the study and for regular monitoring of enrollment across arms. Few previous studies on home and office-based MAT induction have been randomized trials. The study findings will be the result of rigorous research design and methods.

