### *Office-based and Home Induction Protocols*

Standard observed, office-based induction includes the practice staff or clinician assessing the patient for level of withdrawal, administering the first dose of medication, monitoring the patient, and administering subsequent doses of medication at the practice. Patients are given a follow-up plan, including a dosing schedule for the next day, indications of when to call the practice, a follow-up contact schedule (calls or in-person appointment the next day), and an appointment for later in the week.

Standard unobserved, home induction includes giving patients instructions on induction steps. Participants doing home inductions self-assess and determine when they are in adequate withdrawal to administer their first dose of buprenorphine. With home induction, patients administer their initial dose of buprenorphine, assess withdrawal symptoms using the SOWS, and administer subsequent doses of buprenorphine themselves. If practice is aware of when home induction will occur, a member of the practice team might contact patient to assess progress as needed. Patients follow up as agreed upon with their practice team.

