### *Patients*

Interested potential participants (with a diagnosis of OUD and seeking to begin MAT) will receive a study informational packet at their clinic, which will include a copy of the [Postcard Consent Form](#). The practice will call the research team member assigned to them with the patient's contact information for patients that have expressed interest in the study and given the practice permission to initiate contact with the research team. If the patient is interested and willing to learn more at that visit, referred here to as Time 1, the practice will call the research team member assigned to them with the patient's contact information for patients that have expressed interest in the study and given the practice permission to initiate contact with the research team. A member of the research team will describe the study in detail to the patient, confirm eligibility, consent and randomize the patient, and contact the practice with the study arm. If this step cannot occur at Time 1, the practice will transmit to the central study team the interested and eligible patients' contact information for later informed consent and randomization. The goal will be to contact eligible, interested patients within 4 days of Time 1. At what is referred to here as Time 2, the patient will undergo MAT induction, per protocol for the method (home or office-based). We will strive to complete consent and randomization such that practices schedule Time 2 (induction) with 5 – 15 days of Time 1.

A signed, hard copy of the [Postcard Consent Form](#) will not be required from participants. The research team member will obtain and document verbal consent in REDCap. The [Postcard Consent Form](#) will explain that participation is voluntary and that they can discontinue participation at any time, the nature of participation, and that all data are confidential. For children age 16 and 17, we will obtain parent or guardian contact information to contact the parent. Parents or guardians will be informed of the study purposes and procedures. We will contact the child to obtain assent only after consent is obtained from the parent or guardian.

Although patients will be consented, each survey will still include a brief Information Sheet reviewing the conditions of participation, including that participation is voluntary and confidentiality. In addition to documentation of verbal consent by the study team, completion of surveys and assessments will imply consent.

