#### **F. Data Analysis Plan:**

##### *Sample Size and Power:*

We aim to recruit 100 practices, enroll 1200 patients to reach a goal of 1000 patients receiving MAT induction (allowing for attrition prior to MAT induction), and randomize patients evenly to each study arm. For some outcomes (e.g., quality of life), we allow for ~20% attrition (leaving 800 patients total, 400 per arm). Some outcomes will not be affected by patient dropout, so we give a range of sample size estimates. With patient-level randomization, the impact of clustering will be minimal and is not considered here. For the dichotomous outcome of treatment retention, a sample size of 500 patients per arm will provide 81% power to detect a 9% difference in long-term treatment between study arms with  $\alpha=.05$  (e.g., 45% vs 54%). For continuous outcomes (e.g., quality of life, % of days taking buprenorphine out of 270 days), a sample size of 400 to 500 patients per arm will provide 81% power to detect an .18 to .20 SD difference (small) between study arms with  $\alpha=.05$ .

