##### *Quantitative Analytic Plan*

After generating initial descriptive statistics on patient and practice characteristics, we will report on differences between: (1) intervention arms and (2) patient dropouts vs. non-dropouts. We will use an intent to treat analysis to assess the effect of the interventions on long-term treatment. We will examine baseline characteristics of patients in both arms using Pearson’s  $\chi^2$  tests for categorical variables and t-tests for continuous variables to assess for unbalanced confounders. Patient engagement in treatment at 30, 90, and 270 days will be analyzed. Given that the comparators employ different strategies that might affect long-term treatment outcomes, we hypothesize that we will observe a difference in outcomes between the two induction strategies. Patient-level covariates will be screened in bivariate analyses and included in multivariate analysis if related to the outcome at  $p<.2$  or are associated with dropout. Covariates (to adjust for potential confounding) and potential moderators will include age, gender, race/ethnicity, comorbidities, and other sociodemographic and health-related variables.

In the event normality assumptions are not met, we will use transformations to normalize distributions, ordinal or Poisson regression where appropriate, and/or the appropriate link function (e.g. logit link for dichotomized measures). We will employ intent to treat analyses using general (generalized) linear mixed models (GLMMs) to incorporate hierarchical and longitudinal data structures. Hypothesis tests will be two-sided with  $\alpha = .05$  or p values reported. Goodness of fit statistics and model fitting diagnostics will be used to assess influential points, outliers, overdispersion and heteroscedasticity and to evaluate alternative model specifications. All statistical analyses will be performed using SAS version 9.4 (SAS Institute Inc., Cary, N.C.).

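### The protocol randomises about 1200 patients and promises intent to treat, but its sample size, outcome windows and surveys are defined for the roughly 1000 who are later induced, and no rule counts the rest

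*Protocol*

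**What the plan says.** **Order of events.** Under Randomization (section IV.C): "Randomization will occur immediately following consent". The arm is disclosed on the same call. Induction is a later step, described under Consent, Patients: "At what is referred to here as Time 2, the patient will undergo MAT induction". The aim is to schedule it 5 to 15 days after the first visit (Time 1).

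**Numbers.** Sample Size and Power (IV.F) plans to "enroll 1200 patients to reach a goal of 1000 patients receiving MAT induction (allowing for attrition prior to MAT induction), and randomize patients evenly". Participant Recruitment gives the same 1200 and 1000. Power is stated for 500 per arm on the dichotomous outcome and 400 to 500 per arm on continuous outcomes. Randomization to Condition (IV.F) gives about 500 per arm as the result of randomisation.

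**Outcome clock.** The first primary outcome (IV.A) is "Number of days of buprenorphine treatment between day one and day 270 of treatment". The illicit-opioid percentage outcome runs "from induction to nine-month follow-up". The Practice Tracker (IV.D) ties Day 1 to the induction date, and the footnotes to Table 1 time the 30-, 90- and 270-day collections from induction.

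**Analysis principle.** Quantitative Analytic Plan (IV.F): "We will use an intent to treat analysis to assess the effect of the interventions on long-term treatment". The protocol does not say how a randomised patient who is never induced is counted.

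**The concern.** Intent to treat means that every randomised patient is compared in the arm assigned. Here the design quantities describe a different group, those who reach induction. A patient randomised but never induced has no Day 1, no 270-day window and no scheduled follow-up survey.

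Reaching induction happens after randomisation, and the arm can influence it, because the two arms ask different things of the patient before the first dose. If the arms lose different numbers or kinds of patients at this step, those left are no longer comparable by randomisation. H1 and H2 would then be tested on groups formed partly by the treatment under study. The stated power would also belong to a different comparison from the one promised.

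**Working it through.** **1. Size of the gap.** 1200 − 1000 = 200, and 200/1200 = 16.7%. Randomisation follows consent at once, so loss between enrolment and induction is loss after randomisation.

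**2. The plan's own power figure.** Inputs from Sample Size and Power: 45% versus 54%, 500 per arm, α = 0.05; two-sided from the Quantitative Analytic Plan. With p̄ the mean of the two rates,

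power = Φ[(d − 1.96·SE₀)/SE₁], where SE₀ = √(2p̄(1−p̄)/n) and SE₁ = √((p₁(1−p₁) + p₂(1−p₂))/n).

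p̄ = 0.495, SE₀ = 0.03162, SE₁ = 0.03149, so (0.09 − 0.06198)/0.03149 = 0.890 and power = 81.3%. The stated 81% is reproduced. The continuous figures also hold: 0.20 SD at 400 per arm gives 80.7%, and 0.18 SD at 500 per arm gives 81.2%.

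**3. Power for all 600 per arm.** The protocol does not say whether 45% and 54% are rates among the induced or among all randomised, so both readings are shown.

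- *Rates among the induced.* Assume 16.7% loss in each arm, with never-starters counted as not retained. The rates become 0.45 × 5/6 = 37.5% and 0.54 × 5/6 = 45.0%. SE₀ = 0.02842, SE₁ = 0.02834, (0.075 − 0.05571)/0.02834 = 0.681, power 75.2%. Restoring 81% would take 693 per arm (1386 in all). Under other equal loss rates power is 84.4% (5% loss), 80.7% (10%), 72.3% (20%) and 67.8% (25%).
- *Rates among all randomised.* SE₀ = 0.02887, SE₁ = 0.02875, (0.09 − 0.05658)/0.02875 = 1.163, power 87.8%.

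**4. If loss is unequal.** The by-arm splits are assumptions; only the total of 200 is documented. Keep 45% (home) and 54% (office) among the induced:

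| Lost, office / home | All-randomised rates, office / home | Difference |
|---|---|---|
| 120 (20%) / 80 (13.3%) | 43.2% / 39.0% | +4.2 points |
| 150 (25%) / 50 (8.3%) | 40.5% / 41.25% | −0.8 points |
| 80 (13.3%) / 120 (20%) | 46.8% / 36.0% | +10.8 points |

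The same 9-point difference among the induced corresponds to very different all-randomised effects.

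**5. How far an induced-only analysis could mislead.** Suppose there is no true effect, with 225 of 600 (37.5%) reaching 80% of days in each arm, and 540 home but 460 office patients starting. Induced-only rates are 225/540 = 41.7% and 225/460 = 48.9%, a spurious 7.2 points in favour of office, significant in about 63% of trials. With starts of 87% and 79.7% the gap is 4.0 points, significant in about 24%.

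This is an upper-end case, because it makes all 80 extra home starters fail. Suppose instead that office starters succeed at 45% and the extra home starters half as often. The induced-only gap is then 45.0% − 41.7% = 3.3 points for office, significant in about 18% of trials. The all-randomised rates are 207/600 = 34.5% office and 225/600 = 37.5% home, which point the other way. If the extra starters succeed equally often, the induced-only gap is zero. Exchanging the arms reverses every sign.

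**6. Which number is randomised.** Randomization to Condition has an average of 10 patients enrolled per practice. With 100 practices that is 1000, which disagrees with 1200 enrolled.

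**The case against.** The strongest reply is that nothing in the protocol excludes anyone. Intent to treat is stated twice in the Quantitative Analytic Plan, and a scoring rule for never-starters is a detail often left to a statistical analysis plan. For H1 and H2 the data largely exist: the Tracker runs from initial identification and records prescriptions and refills, so zero days and failure to reach 80% could be derived. The sample size section itself says that some outcomes are unaffected by dropout. All of this stands, and it limits the point to a conflict the protocol leaves open. It does not remove the conflict, because the protocol itself fixes the induction-based window, the survey schedule and the 500 per arm. Illicit-opioid self-report and quality of life that were never scheduled for never-starters cannot be recovered by a later analysis plan.

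A reader might infer four stronger things that the protocol does not support:

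- *That never-induced patients are excluded.* No statement says so; it is only what follows if no rule is added.
- *That the bias favours office induction.* Section III says that arriving in withdrawal during office hours is hard. It also says that some patients lack the social support and executive function needed when inducing at home, and that office resources may help motivation and planning. Nothing says which arm loses more.
- *That Day 1 is less well recorded at home.* The words "If practice is aware of when home induction will occur" concern whether staff might contact the patient to check progress. The Tracker asks for the Day 1 date without distinction by arm.
- *That 81% is a calculation error.* It is right for 500 per arm.

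**Conclusion.** The point holds as an internal conflict. Allocation covers about 1200 patients under an intent-to-treat label, while the sample size, outcome windows and survey schedule cover about 1000. As written, this implies that about 200 of 1200 (16.7%) drop out of the comparison unless a rule counts them.

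That an induced-only comparison could be biased rests on the plausible premise that starting treatment depends on the arm. The 63%, 24% and 18% figures show what could happen under assumed start rates and do not predict this trial. For the comparison promised, power is about 75% or about 88%, according to what the 45% and 54% describe; the 75% also assumes equal loss in the two arms.

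**What to change.** - Define the primary population for H1 and H2 as all randomised patients, in the arm assigned.
- Start the 270-day window at randomisation. Count never-induced patients as 0 buprenorphine days and as not reaching 80%.
- Time the 30-, 90- and 270-day surveys and the illicit-opioid self-report from randomisation for every participant, induced or not.
- Report the induced-only analysis as a sensitivity analysis.
- Correct Randomization to Condition, which gives 500 per arm as the result of randomisation, and reconcile the average of 10 per practice with 1200 enrolled.
- Restate power on 600 per arm and say what the rates refer to: about 75% for 37.5% versus 45%, or about 88% if 45% versus 54% apply to all randomised.

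The new anchor is workable. Contact is aimed at within 4 days of Time 1, so the window would end near day 4 + 270 = 274, inside the Tracker's 300-day timeline. Reaching 80% means 0.80 × 270 = 216 days, which leaves 54 days of slack, so the planned wait of up to 15 days does not by itself prevent success.

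The cost is protocol wording, a power statement that may be less favourable, and some added effort to survey patients who never start. It should be settled before enrolment, because follow-up of never-starters cannot be added afterwards.

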##### *Randomization to Condition*

Patients will be randomized to either the office-based MAT induction arm or the home MAT induction arm. An average of 10 patients per practice will be enrolled, with an allowable range of 6 – 20 patients. Block randomization will be used to ensure an equal number of patients in each arm. The “slots” will be randomized for each practice in advance of recruitment to ensure equal distribution between arms at each practice. The result will be approximately 500 patients per study arm. For some outcomes (e.g., quality of life), we allow for ~20% attrition (leaving 800 patients total, 400 per arm).

##### *Quantitative Analytic Plan*

After generating initial descriptive statistics on patient and practice characteristics, we will report on differences between: (1) intervention arms and (2) patient dropouts vs. non-dropouts. We will use an intent to treat analysis to assess the effect of the interventions on long-term treatment. We will examine baseline characteristics of patients in both arms using Pearson’s  $\chi^2$  tests for categorical variables and t-tests for continuous variables to assess for unbalanced confounders. Patient engagement in treatment at 30, 90, and 270 days will be analyzed. Given that the comparators employ different strategies that might affect long-term treatment outcomes, we hypothesize that we will observe a difference in outcomes between the two induction strategies. Patient-level covariates will be screened in bivariate analyses and included in multivariate analysis if related to the outcome at  $p<.2$  or are associated with dropout. Covariates (to adjust for potential confounding) and potential moderators will include age, gender, race/ethnicity, comorbidities, and other sociodemographic and health-related variables.

In the event normality assumptions are not met, we will use transformations to normalize distributions, ordinal or Poisson regression where appropriate, and/or the appropriate link function (e.g. logit link for dichotomized measures). We will employ intent to treat analyses using general (generalized) linear mixed models (GLMMs) to incorporate hierarchical and longitudinal data structures. Hypothesis tests will be two-sided with  $\alpha = .05$  or p values reported. Goodness of fit statistics and model fitting diagnostics will be used to assess influential points, outliers, overdispersion and heteroscedasticity and to evaluate alternative model specifications. All statistical analyses will be performed using SAS version 9.4 (SAS Institute Inc., Cary, N.C.).

We will use general (or generalized) linear mixed models, adjusted for covariates for analysis of primary and secondary outcomes. Even though randomization will be at the patient level, patients are still clustered within practices. Therefore, we will include practice random effects as well as patient random effects (for longitudinal data). Likelihood based models using all available data are the preferred method for analyzing longitudinal data with dropout under MAR conditions. This will be our primary analysis where dropout affects repeated measures over time.

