| Number of days patient took illicit opioids between day 1 and day 270**‡                                                                                  | 
 
▪ Patient self-report of number of days other opioids taken†
 
▪ Patient urine opioid test results‡
 
                                                                                                                   | 
 
▪ Practice Participant Tracker
 
                                                                                                                                                                                                                                                                                                          |
| Took buprenorphine on ≥80% of days between 1 and 270                                                                                      | 
 
▪ Initial prescription and refills†
 
▪ Patient self-report of number of days buprenorphine taken†
 
▪ Patient urine buprenorphine test results‡ (Above data converted to yes/no measure)

 
 | 
 
▪ Practice Participant Tracker
 
                                                                                                                                                                                                                                                                                                          |
| Percent (%) of patients that took other opioids on <10% of days between 1 and 270                                                                         | 
 
▪ Patient self-report of number of days other opioids taken†
 
▪ Patient urine opioid test results‡
 
                                                                                                                   | 
 
▪ Practice Participant Tracker
 
                                                                                                                                                                                                                                                                                                          |

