#### *Specific Tests and Analysis Plans for Outcomes, by Hypotheses*

***H1: Patients using observed (office-based) MAT induction will have a greater number of days of buprenorphine treatment than patients using unobserved (home) MAT induction at nine-month follow-up.***

The outcomes for these analyses will be the total number of days of buprenorphine treatment during the nine-month follow-up period. The structure of the data is hierarchical (patients nested within practices). Intervention is an indicator variable: 0= home-based induction, 1= office-based induction. Covariates will be included in all models but are not shown here for ease of understanding. Since we anticipate the distribution will be over-dispersed, we will not use a Poisson model. Instead, we will first examine the distribution of the outcome data (counts and/or proportions) and explore alternatives such as negative binomial (or possibly beta binomial on proportions), using model diagnostics and goodness of fit measures to select the best approach. For the negative binomial model, modeling counts ( $Y_{ij}$ ) we have

$$\text{Log}(Y_{ij}) = \gamma_{00} + \gamma_{01}(\text{intervention}) + \gamma_{02}(X_{i.}) + u_{0j}$$

where  $\gamma_{00}$  represents the mean (in terms of logs) for home-based induction;  $\gamma_{01}$  represents the difference between means for the office-based vs home induction group;  $\gamma_{02}$  is the effect of patient level covariates on log counts, and  $U_{0j}$  is a practice random effect. Thus, the intervention effect of office-based vs home induction can be tested as  $H_0: \gamma_{01}=0$  vs  $H_1: \gamma_{01}\neq 0$ .

***H2: Patients using office-based MAT induction will be more likely to take buprenorphine on  $\geq 80\%$  of the days between day 1 and day 270 than patients using home MAT induction.***

The outcome for this analysis will be buprenorphine use on  $\geq 80\%$  of days (yes/no). We will use mixed effects logistic regression models (generalized linear mixed models with logit link) to analyze the data. The model will be similar to that shown above, with a random effect for practice and patient level covariates, along with a fixed effect for intervention group.

***H3: Patients using office-based MAT induction will report greater improvement in quality of life, social determinants of health and social functioning over a nine-month follow-up period than patients using home induction.***

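### The no-dropout premise behind the retention power does not match the outcome sources in Table 1, and the stated dropout method does not cover the 270-day totals

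*Protocol*

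**What the plan says.** Protocol section IV.A lists five primary outcomes. Four are a single value per patient over 270 days: "Number of days of buprenorphine treatment between day one and day 270 of treatment", "Number of days of use of illicit opioids between day one and day 270 of treatment", and a yes/no version of each (buprenorphine on at least 80% of days, illicit opioids on under 10%). Only the fifth, quality of life and social functioning, is measured repeatedly.

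For H1, section IV.F states: "The outcomes for these analyses will be the total number of days of buprenorphine treatment during the nine-month follow-up period". The written equation has an intervention effect, patient covariates and a practice random effect. H2 uses a logistic model of the same form. Neither has a time term or a patient effect.

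On dropout, the Quantitative Analytic Plan says: "Likelihood based models using all available data are the preferred method for analyzing longitudinal data with dropout under MAR conditions". It then sets the scope: "This will be our primary analysis where dropout affects repeated measures over time".

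The Sample Size and Power section says: "Some outcomes will not be affected by patient dropout, so we give a range of sample size estimates". It does not name those outcomes. It allows about 20% attrition (400 per arm) for outcomes such as quality of life, but gives the retention power only at 500 per arm.

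Table 1 gives refills and self-report as sources for buprenorphine days, and adds urine buprenorphine tests for the 80% outcome. For both illicit-opioid outcomes the sources are "Patient self-report of number of days other opioids taken" and urine opioid tests. No order of precedence is given.

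**The concern.** The premise that dropout leaves an outcome untouched depends on where that outcome's data come from. Refill records can be completed by the practice after a patient stops answering. Self-report cannot, and urine tests need a visit. Every day-based primary outcome in Table 1 uses at least one source that ends with patient contact, and the illicit-opioid outcomes use only such sources.

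A model with one row per patient has no earlier measurements to draw on. If a patient's total cannot be formed, that patient contributes nothing, even when 30-day or 90-day reports exist. Leaving care in itself lowers buprenorphine days, so the missing patients are unlikely to resemble the rest.

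The obvious shortcut also misleads. Suppose a patient reports 10 illicit days and is lost at day 60. If unobserved days were scored as zero, the result is 10/270 = 3.7%, a success on the under-10% outcome, although use over the observed period was 10/60 = 16.7%.

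**Working it through.** **1. The plan's own power.** Inputs from Sample Size and Power: 45% versus 54%, two-sided alpha 0.05, n per arm.

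Power = Φ{[|p₂−p₁| − 1.96·√(2p̄(1−p̄)/n)] / √([p₁(1−p₁)+p₂(1−p₂)]/n)}, with p̄ = 0.495.

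- n = 500: (0.09 − 1.96×0.03162)/0.03149 = 0.890, power 81.3%. The stated 81% is reproduced.
- n = 450 (10% loss, assumed): 77.1%.
- n = 400 (the plan's 20% loss): (0.09 − 1.96×0.03535)/0.03521 = 0.588, power 72.2%.

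The last two keep 45% and 54% among the patients analysed, so they assume loss unrelated to outcome.

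For continuous outcomes, power = Φ(d·√(n/2) − 1.96). This gives 81.2% at 500 per arm and 0.18 SD, and 80.7% at 400 per arm and 0.20 SD, both as stated. At 400 per arm and 0.18 SD it is 72.1%.

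**2. Sources and methods side by side.**

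| Primary outcome | Sources (Table 1) | Source that survives loss of contact | Reached by the stated dropout method |
|---|---|---|---|
| Buprenorphine days | refills, self-report | refills | no, one total |
| Buprenorphine ≥80% | prescriptions and refills, self-report, urine | refills | no, one yes/no |
| Illicit-opioid days | self-report, urine | none | no, if one total |
| Illicit opioids <10% | self-report, urine | none | no, if one yes/no |
| Quality of life | surveys | none | yes, repeated |

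**3. Possible bias, ≥80% outcome.** Assumed: true rates 45% home and 54% office; a fraction d is lost per arm; a fraction r of those lost truly reached 80%. Rate among those analysed = (p − d·r)/(1 − d). With r = 0:

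- Equal loss, 20% and 20%: 0.45/0.80 = 56.25%, 0.54/0.80 = 67.5%, difference 11.25 points against a true 9.
- Loss 25% home, 15% office: 0.45/0.75 = 60.0%, 0.54/0.85 = 63.5%, difference 3.5 points. It is 6.7 if r = 0.20 and 10.6 if r = 0.45.
- Loss 15% home, 25% office: 52.9% and 72.0%, difference 19.1 points.

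With no true difference (49.5% in both arms) and loss of 25% home and 15% office, the analysed rates are 66.0% and 58.2% if r = 0 (rejection rate 62%), or 59.3% and 54.7% if r = 0.20 (rejection rate 26%). With equal 20% loss the rejection rate stays at 5%.

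**4. Possible bias, illicit-opioid days.** Assumed: 10 days if retained, 150 if not, with all loss among the non-retained. Truth: home 0.45×10 + 0.55×150 = 87.0; office 0.54×10 + 0.46×150 = 74.4; difference −12.6 days.

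- Equal loss, 20% and 20%: home (4.5 + 0.35×150)/0.80 = 71.25; office (5.4 + 0.26×150)/0.80 = 55.5; difference −15.75.
- Loss 25% home, 15% office: (4.5 + 0.30×150)/0.75 = 66.0; (5.4 + 0.31×150)/0.85 = 61.1; difference −4.9.
- Loss 15% home, 25% office: (4.5 + 0.40×150)/0.85 = 75.9; (5.4 + 0.21×150)/0.75 = 49.2; difference −26.7.

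None of the inputs in steps 3 and 4 is in the protocol, apart from 45%, 54% and the overall 20%.

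**The case against.** The protocol does not misapply its likelihood method. It confines it to repeated measures, so a reader who infers that a wrong method is used for the totals goes too far. Nor is a one-row model invalid as such: it is sound if missingness depends only on arm and included covariates, and the Quantitative Analytic Plan brings in covariates associated with dropout. That helps, but it does not remove dependence on the unobserved outcome itself.

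The buprenorphine outcomes are well protected in principle. The Practice Participant Tracker holds prescriptions, refills and whether treatment continues, and monthly calls collect drop-out information, so a patient who stops can have an observed low total. This stands. What is missing is a statement that these records decide the outcome.

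A reader might also infer that the protocol calls the illicit-opioid outcomes immune to dropout, or that it prescribes a complete-case analysis. It says neither. The unaffected outcomes are left unnamed, the analysis is described as intent to treat, and detailed rules for missing totals may sit in a statistical analysis plan that is not at hand. The finding rests on what this document does fix: the premise, the sources and the single-value models.

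The continuous power range already runs from 400 to 500 per arm, so only the retention figure stands on no loss. Finally, the 20% allowance leaves 400 in each arm, which is equal loss and the milder case. The timing mark on the self-report entries is missing from Table 1's legend, possibly through text extraction. However, the row for illicit-opioid days carries the mark for baseline, 30, 90 and 270 days.

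**Conclusion.** The concern holds as a mismatch and a gap in coverage. The no-dropout premise is true for the buprenorphine outcomes only if refill and discontinuation records decide them, which Table 1 does not say. No listed source supports it for the illicit-opioid outcomes. The stated dropout method leaves the H1 and H2 totals, and a single illicit-opioid total, without cover.

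If the plan's 20% loss applied to retention and were unrelated to outcome, power would be about 72% rather than 81%. If loss is related to outcome, the larger issue is bias. Under the assumptions shown, a true 9-point difference could appear as anything from 3.5 to 19.1 points, with 11.25 under equal loss. A true −12.6 illicit days could appear as −4.9 to −26.7, with −15.75 under equal loss. These figures show direction and scale and are not forecasts. Under no true difference, false rejection arose with unequal loss and not with equal loss. The point is worth settling before the analysis is fixed, and the illicit-opioid outcomes are the most exposed.

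**What to change.** 1. **Buprenorphine outcomes (H1, H2).** Make prescription and refill supply, with the Tracker's discontinuation status, the primary source for every randomised patient through day 270. Use self-report and urine as supporting or sensitivity measures. State how day 1 is set for a patient randomised but never induced, since the protocol expects attrition before induction. If this source is not adopted, restate the retention power with attrition.

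2. **Illicit-opioid outcomes.** Analyse counts for days 1–30, 31–90 and 91–270 (30 + 60 + 180 = 270) in a mixed model with a log(days) offset and patient and practice random effects. Partial follow-up then contributes under the protocol's own preferred method. Add a sensitivity analysis that counts unobserved days as use days. Apply both to the under-10% outcome as well, for example by imputing missing intervals from the same model before classifying.

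3. **Sample Size and Power.** Limit the no-dropout premise to the refill-based buprenorphine outcomes and name them.

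The cost is wording and some programming, as data at 30, 90 and 270 days are already planned. There is a small downside: the outcome becomes days supplied rather than days taken, and a patient who moves to another prescriber counts as off treatment unless the Tracker shows otherwise. For scale, with loss of 25% home and 15% office, if 20% of those lost had in fact reached 80%, scoring them all as failures gives (0.54 − 0.03) − (0.45 − 0.05) = 11.0 points instead of 9.
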